### Randomization, allocation, and blinding

Participants will be randomly assigned in a 1:1 ratio to the intervention (BIP) or waitlist control group using a computer-generated sequence with permuted blocks (undisclosed block sizes) created by a researcher not involved in recruitment or intervention delivery. Allocation will be concealed until assignment, after which participants will be informed of their group by the study coordinator via email.

This is an open-label trial; neither participants nor facilitators will be blinded to group assignment. Given the behavioral nature of the intervention, blinding of participants and facilitators was not feasible. To minimize bias, outcomes will be collected via standardized electronic self-report measures, and datasets provided to the analysis team will be de-identified.

### Sample size and statistical analysis

This pilot RCT aims to recruit 30 participants in total, with 15 allocated to the intervention arm and 15 to the waitlist control. Participants in the intervention condition will be organized into two groups of approximately 7–8 participants each, consistent with recommendations for small-group delivery of the BIP. This sample size is a pragmatic target aligned with recommendations for external pilots, where small samples are sufficient to assess feasibility and provide preliminary estimates for future trials (24, 27, 41). The study is therefore not powered for hypothesis testing; the focus is on feasibility and preliminary effect estimation.

Analyses will follow an intention-to-treat approach. All randomized participants will be invited to complete T2 and T3 assessments, including those who discontinue the intervention or withdraw from other study activities. Analyses will include all randomized participants under the ITT framework, with exploratory per-protocol analyses limited to participants who attend both sessions. Continuous outcomes (ED-15 and secondary measures) will be examined using linear mixed-effects models with Group, Time, and their interaction as fixed effects, and a random intercept for participants. Between-group differences in change from baseline to post-intervention and follow-up will be reported with 95% confidence intervals and standardized effect sizes. Missing data will be handled using maximum likelihood estimation within the mixed-effects models, which accommodate incomplete data under a missing-at-random (MAR) assumption. Feasibility outcomes (recruitment, retention, adherence, satisfaction) will be summarized descriptively with proportions and 95% CIs. All analyses will be conducted in R (R Core Team).

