### Intervention

Participants randomized to the intervention arm will receive the BIP, a culturally adapted, dissonance-based group intervention derived from the Body Project (21, 30). Cultural adaptations include (a) linguistic modifications for Mexican Spanish, (b) replacement of U.S.-centric appearance examples and media imagery with locally relevant content, (c) incorporation of sociocultural pressures specific to Latin American beauty ideals, such as the curvy-thin ideal and the normalization of appearance-based teasing, and (d) culturally relevant behavioral challenges that target real-life situations common among Mexican university students. Additionally, the intervention was renamed as the Body Image Program (BIP) to improve clarity and acceptability in Spanish-speaking contexts, while preserving the theoretical foundation and session structure of the original Body Project. These adaptations were developed and evaluated in prior BIP implementation studies in Mexico and Latin America (21), which demonstrated feasibility and acceptability, but did not include randomization or a control group. The program consists of two 120-minute group sessions, delivered once per week over two consecutive weeks, in small groups of 7–10 participants (maximum 10). When the intervention arm exceeds one group’s capacity, participants will be scheduled into two concurrent groups of approximately 7–10 each to preserve group processes and logistics. Sessions include verbal, written, and behavioral exercises to elicit cognitive dissonance, critically evaluate sociocultural appearance ideals, and foster more adaptive body-image perspectives. A session-by-session overview is provided in **Table 1**.

**Table 1 T1:** Overview of the Body Image Program (BIP): objectives, core activities, and homework.

Session	Main objectives	Core activities	Homework assignments

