The intervention will be delivered by trained health professionals (Group Leaders) with prior experience in eating disorders, who have completed the standardized BIP training program and receive ongoing supervision to ensure adherence to the protocol. The standardized BIP training follows a train-the-trainer model and includes approximately 16 hours of experiential instruction combining theoretical foundations, practice-based demonstrations, and supervised mock sessions to ensure facilitator proficiency (21). Fidelity will be monitored through session checklists completed by Group Leaders and periodic supervision meetings with senior BIP trainers. If pre-session attrition reduces a group below seven participants, sessions may be rescheduled or participants reassigned to maintain the minimum group size. The program will be delivered in Spanish using culturally adapted materials developed in prior implementation studies in Mexico and Latin America (21).

Each session concludes with homework designed to reinforce dissonance-based learning. These tasks are considered part of participant engagement but will not be included in the definition of adherence, which is based on attendance to the two intervention sessions. After Session 1, participants receive structured tasks (e.g., a behavioral challenge, reflective writing, mirror exercise). At the end of Session 2, a commitment assignment is provided (e.g., self-affirmation or body-activism activity) intended to consolidate program principles during the weeks prior to follow-up. Participants are asked to complete this final assignment within one week of Session 2 and to submit it by email to the Group Leaders, ensuring engagement during the immediate post-intervention period.

Participants allocated to the waitlist control condition will complete the same assessment schedule as the intervention group (T1, T2, T3) but will not receive any intervention during the study period. After the final follow-up assessment (T3, week 6), they will be offered the BIP between weeks 6 and 8, in line with ethical considerations and the principle of post-trial access for control participants. This approach is consistent with the principles of the Declaration of Helsinki, which emphasize that participants in control conditions should not be denied access to potentially beneficial interventions once the main study assessments are completed (42).

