### Facilitator training

Each session will be delivered by two trained Group Leaders, who are health professionals with prior experience working with eating disorders. All leaders must have completed the standardized BIP training program conducted by headmaster trainers. The training follows an experiential approach that integrates theoretical foundations with practice in both facilitator and participant roles, ensuring the development of technical competencies and a comprehensive understanding of group processes. Leaders also receive ongoing supervision during implementation, which supports fidelity to the intervention protocol, consistency across groups, and effective management of group dynamics.

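### The stated mixed model ignores that only the BIP arm is delivered in groups, so between-group intervals for change are too narrow to the extent that outcomes correlate within those groups

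*Protocol article*

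**What the plan says.** Under Sample size and statistical analysis, the protocol "aims to recruit 30 participants in total, with 15 allocated to the intervention arm and 15 to the waitlist control". The same section states: "Participants in the intervention condition will be organized into two groups of approximately 7–8 participants each". The Intervention section explains the split: when the arm is too large for one group, "participants will be scheduled into two concurrent groups of approximately 7–10 each to preserve group processes and logistics". It also allows participants to be moved if a group falls below seven. Under Facilitator training: "Each session will be delivered by two trained Group Leaders". Waitlist participants "will not receive any intervention during the study period", so they form no delivery groups between T1 and T3.

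The continuous outcomes are to be analysed with "linear mixed-effects models with Group, Time, and their interaction as fixed effects, and a random intercept for participants". The product of that model is stated as follows: "Between-group differences in change from baseline to post-intervention and follow-up will be reported with 95% confidence intervals and standardized effect sizes". On estimation: "Missing data will be handled using maximum likelihood estimation within the mixed-effects models".

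No section mentions delivery group as a source of variation, an ICC, or a partially nested model. The Discussion says that variability seen in the pilot will feed the sample size of the full trial.

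**The concern.** Women in the same BIP group share its discussions, exercises and sessions, and the protocol treats group cohesion and group processes as part of how the programme works. Their post-session scores may therefore move together. Waitlist participants have no such shared exposure. A participant intercept accounts for repeated measures on one person, but not for a shift common to seven or eight people after baseline. The random-effects structure is stated outright, so this is not a detail left open for an analysis plan, and it does not match the delivery described in the same section.

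The stake is the stated precision of the clinical results. The trial renounces hypothesis testing and offers effect estimates with intervals instead, so the width of those intervals is how it conveys uncertainty about ED-15 and the secondary scales.

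**Working it through.** **Inputs from the protocol.** 15 participants per arm; BIP groups of 7 and 8 (7 + 8 = 15); no waitlist groups; three time points; the contrast is the difference in change from baseline. The total of 30 is a pragmatic target with no power formula behind it, so the only figures to reproduce are 15 + 15 = 30 and 15/2 = 7.5, which agree with the text.

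**Assumptions not in the protocol.** ICC of 0 to 0.10 at T2 and T3; within-person correlation ρ of 0.7, varied to 0.5 and 0.8; complete data; a group effect that arises after baseline and is the same at T2 and T3.

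**Standard error of the difference in change.** Set the variance of one participant's score, without the group effect, to 1.

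- Independent part: 2(1 − ρ)(1/15 + 1/15). At ρ = 0.7 this is 2 × 0.3 × 0.1333 = 0.0800.
- Group part: σ²_g × (7² + 8²)/15² = σ²_g × 113/225 = 0.5022 σ²_g, with σ²_g = ICC/(1 − ICC).
- Ratio of true SE to independence SE: √[(0.0800 + group part)/0.0800].

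| ICC | σ²_g | Group part | Total | SE ratio |
|---|---|---|---|---|
| 0 | 0 | 0 | 0.0800 | 1.000 |
| 0.01 | 0.0101 | 0.0051 | 0.0851 | 1.031 |
| 0.02 | 0.0204 | 0.0102 | 0.0902 | 1.062 |
| 0.05 | 0.0526 | 0.0264 | 0.1064 | 1.153 |
| 0.10 | 0.1111 | 0.0558 | 0.1358 | 1.303 |

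The fitted model absorbs a little of the group variance into its residual. In simulation the true SE exceeds the model's own SE by about 3%, 6%, 15% and 29%.

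**Coverage of the nominal 95% interval.** The random-intercept model was simulated with at least 100,000 data sets per setting. The residual variance was estimated by REML and the limits used t with 56 degrees of freedom, which isolates the effect of grouping. Ranges show repeated runs.

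| ICC | Coverage at ρ = 0.7 |
|---|---|
| 0 | 94.9–95.0% |
| 0.01 | 94.3–94.6% |
| 0.02 | 93.6% |
| 0.05 | 91.3–91.6% |
| 0.10 | 87.3–87.6% |

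At ICC 0.05, coverage is about 93% for ρ = 0.5 and 89.4–89.9% for ρ = 0.8. With ML variances and normal limits, coverage at ρ = 0.7 is 93.6% even at ICC 0 and 89.7% at ICC 0.05. The first of those shortfalls is a small-sample matter separate from grouping.

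**Why the usual design effect understates this.** For a single post-score comparison, the BIP arm's design effect is 1 + (7.53 − 1) × ICC, where 7.53 = 113/15, and the SE ratio is √[(1 + design effect)/2]. This gives 1.016, 1.032, 1.079 and 1.152 at the four positive ICCs. The protocol reports change. Subtracting baseline removes stable differences between people but leaves a group effect that arose later, so the proportional loss is larger.

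**The case against.** The strongest reply is that no ICC is given and none is known to be positive. That stands. A reader might infer that every between-group interval is too narrow, but the documents do not support this: at ICC 0 the stated model covers at its nominal rate, and at 0.01–0.02 the loss is only about half a point to a point and a half at ρ = 0.7. The defect is an unstated assumption of zero correlation, in a programme that relies on its groups, rather than a demonstrated error in each interval.

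Second, this is a pilot. The Discussion puts feasibility and acceptability ahead of efficacy, and warns that clinical findings are preliminary and effect sizes may be unstable. That limits the severity, but a general warning about sample size does not tell a reader that the printed intervals leave out a source of variance.

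Third, two groups provide one degree of freedom, so a fitted group variance would often be zero or erratic. This is correct. It rules out simply adding a random effect and estimating it, but not intervals at fixed ICCs. A condensed article may leave sensitivity analyses to a fuller document. Here, however, the article itself fixes the random-effects structure.

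Two further inferences should be resisted. The Discussion does not say that the definitive trial will be sized without regard to grouping; it names variability and attrition and gives no formula. Nor does the protocol say whether the two groups have different leaders, so a leader effect cannot be separated from a group effect or assumed.

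**Conclusion.** The concern holds in conditional form. The stated model does not match the partially nested delivery, and the between-group intervals for change in ED-15 and the secondary scales understate uncertainty in proportion to any within-group correlation. The effect is negligible at an ICC near zero, modest at 0.02 and material at 0.05–0.10. These sizes rest on an assumed ICC, an assumed within-person correlation and complete data. A higher within-person correlation makes the loss worse and a lower one makes it milder.

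The severity is should-fix. Point estimates are not biased by the omission, the feasibility proportions and their thresholds are untouched, and no confirmatory test depends on these intervals.

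**What to change.** 1. Record the delivery group that each BIP participant actually attended, including any move made under the Intervention section's rule on minimum group size. This has to be captured during conduct.
2. Keep the planned model. Beside it, report partially nested intervals for the T2 and T3 contrasts, with a group effect in the BIP arm only and after baseline only, and the ICC fixed at 0.01, 0.02, 0.05 and 0.10. Do not estimate the group variance from two groups.
3. Describe the planned-model intervals as conditional on no within-group correlation.
4. Where pilot variability is carried forward to size the definitive trial, note that it contains no allowance for grouping.

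The cost is a few lines of analysis text and R code, one extra variable, and wider intervals in the sensitivity table. No change to sample size, delivery or assessments is needed.

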### Outcomes and measures

Feasibility and acceptability outcomes will be assessed following guidance for pilot RCTs (24, 27). Recruitment will be indexed as the proportion of eligible students who consent and are randomized, with ≥70% considered acceptable. Retention will be measured as the percentage completing T2 and T3 assessments, with a target of at least 80%. Adherence will be defined primarily as attendance, categorized per participant as full (2/2 sessions), partial (1/2), or none (0/2), with ≥70% full adherence considered acceptable. Submission of the Session-2 commitment task within one week will be examined separately as an indicator of engagement, consistent with the preregistered protocol, and will be reported independently from adherence. Acceptability will be evaluated through a brief post-intervention survey at T2 on usefulness, clarity, and relevance, with favorable acceptability defined *a priori* as a mean rating ≥4 on a 5-point scale. Feasibility indicators will be summarized descriptively using percentages and 95% confidence intervals, without formal hypothesis testing.

The primary clinical outcome will be change in eating disorder symptoms, assessed with the Eating Disorder-15 (ED-15; 31), a 15-item self-report instrument that evaluates core symptoms over the past week. Items are rated on a 0–6 Likert scale and yield two subscales (Eating Concerns; Weight/Shape Over-evaluation), as well as a total score calculated as the mean of all items. Possible values range from 0 to 6, with higher scores indicating greater eating disorder symptom severity. A recent validation study in a Mexican clinical sample supported its factorial structure, internal consistency, and convergent validity (32).

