Secondary outcomes will address constructs consistent with sociocultural and cognitive-behavioral models of eating disorder risk and protection. BD will be assessed with the Body Shape Questionnaire-8 (BSQ-8; 33), with evidence of validity in Spanish-speaking populations (34). Scores range from 8 to 48, with higher values indicating greater dissatisfaction. Positive body image will be measured with the Body Appreciation Scale-2 (BAS-2; 23), which has demonstrated measurement invariance and reliability in Latin American adolescents (35); the BAS-2 consists of 10 items rated from 1 to 5, with higher scores reflecting greater body appreciation. Social physique anxiety will be assessed with the Social Physique Anxiety Scale-7 (SPAS-7; 22), supported by evidence of reliability and validity in Spanish-speaking samples (36); scores range from 1 to 5, with higher values indicating greater anxiety in social contexts. Internalization of sociocultural appearance ideals will be measured with the Thin-Ideal Internalization subscale of the Sociocultural Attitudes Towards Appearance Questionnaire-4 (SATAQ-4; (37), which has been culturally adapted and validated in Latin American populations (38). This subscale includes 5 items rated from 1 to 5, with higher scores indicating stronger thin-ideal internalization. Finally, appearance-related social comparisons will be evaluated with the Physical Appearance Comparison Scale (PACS; (39), with validation evidence in Spanish-speaking populations (40). Items are rated on a 5-point Likert scale from 0 (never) to 4 (always), and higher mean scores indicate more frequent appearance-based comparisons.

All self-report instruments will be administered at baseline (T1, week 0), post-intervention (T2, week 2), and 4-week follow-up (T3, week 6).

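### The random-intercept model with free baseline means makes limited use of the T1 score and gives T2 and T3 essentially one standard error; a common T1 mean with visit-specific covariance would serve 15 per arm better

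*Protocol article*

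**What the plan says.** All of this is in Sample size and statistical analysis unless another section is named.

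- **Size.** "This pilot RCT aims to recruit 30 participants in total, with 15 allocated to the intervention arm and 15 to the waitlist control". The target is pragmatic, and "The study is therefore not powered for hypothesis testing; the focus is on feasibility and preliminary effect estimation".
- **Model.** ED-15 and every secondary measure are analysed with "linear mixed-effects models with Group, Time, and their interaction as fixed effects, and a random intercept for participants".
- **Reported quantity.** "Between-group differences in change from baseline to post-intervention and follow-up will be reported with 95% confidence intervals and standardized effect sizes".
- **Incomplete data.** "Missing data will be handled using maximum likelihood estimation within the mixed-effects models", under a missing-at-random assumption.
- **Timing.** Outcomes and measures places the self-report assessments at weeks 0 (T1), 2 (T2) and 6 (T3). The same section makes ED-15 the primary clinical outcome.

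The article thus fixes the fixed effects, the random effect and the contrast. It describes no baseline adjustment, no equal-baseline constraint and no covariance that varies by visit.

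**The concern.** Two features of the written model matter at this sample size.

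First, a Group main effect that applies at T1 lets the two arms have different baseline means. Randomisation says that they share one. The Group×Time contrast then subtracts the whole baseline difference instead of the part that predicts the later score. That is the best use of baseline only when ρ, the correlation between baseline and the later score, is 1.

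Second, a random intercept alone assumes equal variances and the same correlation for T1–T2 (2 weeks), T2–T3 (4 weeks) and T1–T3 (6 weeks). With complete data, the T2 and T3 contrasts then carry exactly the same standard error. If scores six weeks apart agree less well than scores two weeks apart, that pooled error is wrong for at least one of the two visits.

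With no powered test, the intervals for ED-15 and the secondary measures are the clinical result of the pilot. A fit with one variance and one correlation also cannot show whether correlation falls with time.

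**Working it through.** **Inputs.** From the article: n = 15 per arm, three visits, the model and contrast above. The article gives no SD and no within-person correlation, so the SD is set to 1 and the correlations are assumptions shown over a range. There is no power or precision calculation in the article to reproduce.

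**Step 1: large-sample precision, equal variances.**

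- Planned contrast: SE = √(2(1−ρ)·2/n)
- Baseline-adjusted contrast: SE = √((1−ρ²)·2/n)
- Ratio of variances: (1−ρ²)/(2(1−ρ)) = (1+ρ)/2

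| ρ | Planned SE | Adjusted SE | Variance ratio |
|---|---|---|---|
| 0.5 | 0.365 | 0.316 | 0.75 |
| 0.7 | 0.283 | 0.261 | 0.85 |
| 0.8 | 0.231 | 0.219 | 0.90 |
| 0.9 | 0.163 | 0.159 | 0.95 |

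Ignoring baseline altogether gives √(2/15) = 0.365. At ρ = 0.5 the planned contrast is therefore no more precise than a comparison of later scores alone.

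**Step 2: the same comparison with small-sample limits.** These are simulated complete trials, 15 per arm, equal correlation true. The planned model uses REML and t limits on 56 df. Adjustment is represented by ANCOVA at each visit (27 df), which pays for estimating the slope.

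| ρ | Planned half-width | ANCOVA half-width | Change |
|---|---|---|---|
| 0.5 | 0.728 | 0.655 | −10% |
| 0.7 | 0.564 | 0.540 | −4% |
| 0.8 | 0.461 | 0.454 | −1.5% |
| 0.85 | 0.399 | 0.398 | nil |
| 0.9 | 0.326 | 0.330 | +1% |

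**Step 3: the shared standard error.** With complete data and equal variances, the random-intercept fit in effect uses the mean of the three correlations, r̄, at both visits: SE ≈ √(2(1−r̄)·2/15). The true SE at a visit uses that visit's own correlation with T1. For 0.8/0.6/0.7 (T1–T2/T1–T3/T2–T3), r̄ = 0.7:

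- model SE at both visits: √(0.6 × 0.1333) = 0.283
- true SE at T2: √(0.4 × 0.1333) = 0.231
- true SE at T3: √(0.8 × 0.1333) = 0.327

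**Step 4: coverage of nominal 95% intervals, planned model with REML and t limits (simulated).**

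| Correlations T1–T2/T1–T3/T2–T3 | T2 | T3 |
|---|---|---|
| Equal (0.5 or 0.7) | 95% | 95% |
| 0.75/0.70/0.75 | 96% | between 93% and 94% |
| 0.8/0.7/0.8 | 96.5% | 92% |
| 0.8/0.6/0.7 | 98% | 91% |
| 0.7/0.6/0.8 | 95% | 91% |

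ANCOVA at each visit covered about 95% at T2 and T3 throughout. Under 0.8/0.6/0.7 its half-widths are 0.454 at T2 and 0.605 at T3, against 0.563 at both visits for the planned model. There the change narrows the T2 interval and correctly widens the T3 interval.

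**Step 5: missing data.** The standard errors are identical only with complete data. In 300 fits under 0.8/0.6/0.7 with 10% missing at T2 and 20% at T3, the model SEs (maximum likelihood) were 0.278 and 0.291, against true values of about 0.24 and 0.35. Most of the distortion remained.

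**The case against.** The strongest reply is that this is a standard and legitimate model in a trial that claims no power. The Discussion puts feasibility and acceptability, not efficacy, first and treats clinical findings as preliminary. The correlations are not in the article. If they are equal across visits, REML with t limits covers 95%, and if they are about 0.85 or higher, baseline adjustment gains nothing. All of that stands, and it limits the weight of the point.

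A reader might also infer more than the document supports:

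- **That maximum likelihood is itself an error.** The phrase occurs only in the missing-data sentence, where it explains why incomplete cases can be kept. It need not exclude REML, and normal-theory limits are stated nowhere. The choice of estimator and degrees of freedom is commonly left to an analysis plan.
- **That chance baseline imbalance biases the contrast.** Under randomisation the change contrast is unbiased. The shift caused by an imbalance is the excess variance already counted in (1+ρ)/2.
- **That adjustment is worth 40 or 35 participants for the price of 30.** That divides 30 by 0.75 or 0.85 and ignores the cost of estimating the slope and the fewer degrees of freedom. The half-widths in Step 2 are the fair measure.
- **That the definitive trial would be wrongly sized.** The Discussion bases that size on variability and attrition. The standard error of a contrast is not the outcome SD, and no bias in the SD has been shown.

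**Conclusion.** The point holds as a moderate improvement to a model that the article states explicitly. The free T1 means cost about 10% of interval half-width at ρ = 0.5, 4% at 0.7, 1–2% at 0.8 and nothing from about 0.85. The equal-correlation assumption does no harm if it is true. If correlation decays over the six weeks, T3 intervals are too short, covering about 91–94% in the patterns tried, and T2 intervals are usually too wide, covering 96–98%. T2 is not always too wide: at 0.7/0.6/0.8 it covers 95%.

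It would go too far to call the planned intervals miscalibrated as a matter of fact, since that rests on correlations the article does not give. These sizes assume equal variances across visits and, apart from the small missing-data check, complete data. Feasibility results are untouched; the effect is confined to the ED-15 and secondary-outcome contrasts.

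**What to change.** For ED-15 and each secondary outcome, replace the model sentence with one specifying:

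- T1, T2 and T3 scores as outcomes, with a common T1 mean for both arms (Time plus Group×post-baseline Time, no Group effect at T1);
- unstructured within-participant covariance (three variances and three correlations, so six parameters);
- REML with Kenward-Roger degrees of freedom;
- T1 completed before the allocation email is sent. The common T1 mean relies on this in an open-label trial, whereas the current model does not;
- if the model does not converge, ANCOVA at each visit on the T1 score.

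**Cost.** A change of wording and a standard R package, with no new data or participants. Intervals would be slightly wider if correlations are equal and about 0.85 or higher (0.330 against 0.326 at ρ = 0.9). The ANCOVA fallback loses the T2 information of participants who miss T3, so it should remain a fallback.
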